## Abstract

**Background:**

The prevalence of overweight and obesity remains high in Canada, and the current standard for the treatment of childhood obesity is in-person, family-based, multidisciplinary interventions that target lifestyle behaviors (e.g., diet, physical activity, and sedentary behaviors). These programs are costly to operate, have limited success, and report recruitment and retention challenges. With recent advances in technology, mobile health or mHealth has been presented as a viable alternative to in-person interventions for behavior change, especially with teens.

**Purpose:**

The primary aim of this study is to test the efficacy of Aim2Be, a gamified app based on behavior change theory with health coaching to improve weight outcomes (i.e., decrease in standardized body mass index (zBMI)) and lifestyle behaviors (i.e., improve dietary quality, increase fruit and vegetable intake, reduce sugar-sweetened beverage intake, increase physical activity, and reduce screen time) among children 10- to 17-years old with overweight or obesity versus their peers randomized into a waitlist control condition. The secondary aims of this study are to 1) test whether supplementing the Aim2Be program with health coaching increases adherence and 2) examine the mediators and moderators of adherence to the Aim2Be intervention.

**Methods:**

We will employ a randomized controlled trial design and recruit 200 child and parent dyads to participate in the study (2019–2020). Participants will be recruited from Canadian pediatric weight management clinics and through online advertisements. Child participants must be between the ages of 10 and 17 years, have overweight or obesity, be able to read English at least at a grade 5 level, and have a mobile phone or home computer with internet access. Following baseline data collection, participants will be randomized into intervention and waitlist control groups. Intervention participants will receive access to Aim2Be, with access to health coaching. After having their data collected for 3 months, the control group will gain access to Aim2Be, with no access to health coaching. Participants will control their frequency and duration of app usage to promote autonomy.

**Discussion:**

Findings from this study will determine the efficacy of using Aim2Be in improving child weight outcomes and lifestyle behaviors and guide future mHealth interventions for pediatric weight management.

**Trial registration:**

ClinicalTrials.gov, NCT03651284. Registered 29 August 2018.

## Background

In Canada, approximately one-third of children aged 5–17 years have either overweight (19.8%) or obesity (11.7%) [1]. As children with overweight or obesity grow, they are more likely to develop a host of health issues including cardiovascular risk factors, Type 2 diabetes, asthma, sleep apnea, joint pain, and mental health issues [2–6]. Furthermore, numerous reports have shown that childhood obesity tracks into adulthood [7, 8], highlighting the need to develop efficacious and accessible lifestyle interventions for children and teens.

The causes of childhood obesity are complex and multifactorial [9]. Currently, the accepted standard of care for the management of childhood obesity is to provide in-person, family-based, multidisciplinary interventions that target lifestyle behaviors (e.g., diet, physical activity, and sedentary behaviors) and behavioral strategies at both the individual and familial levels [10, 11]. While such strategies are efficacious at decreasing weight or the body mass index (BMI) z-score [10, 11], their effects are modest, not sustained, and high attrition is a common problem [12–16]. In a German study that included 21,784 children attending a community weight management program, 76% and 92% of the participants dropped out after 6 and 24 months, respectively [14]. If these pediatric weight management interventions are going to achieve optimal impact for children and their families, the development and evaluation of more novel and engaging interventions that can meet the needs of these families and improve health outcomes are needed [17].

Mobile health (mHealth) technologies provide an opportunity to bring weight management interventions directly to individuals and to deliver such interventions on an ongoing basis throughout the day [18]. In children, mHealth interventions have predominantly targeted 12- to 15-year-olds, although some studies have included 15- to 19-year-olds [19]. Data on the efficacy of mHealth interventions for managing childhood obesity is still emerging [19, 20]. Importantly, mHealth interventions are ideally suited to 1) address some of the barriers associated with in-person lifestyle behavior modification interventions including the lack of enthusiasm for in-person meetings, lack of financial resources, inconvenient location, and lack of time [12, 15, 21, 22]; 2) emphasize the development of self-regulatory skills (e.g., goal setting, planning, and self-monitoring) that are hallmarks of effective lifestyle behavioral modification interventions [11], as specific app features can be designed to support self-regulatory processes; and 3) improve engagement by incorporating game-design elements without the context of what is traditionally considered a “game“ [23]. A review by Johnson et al. [24] identified that gamification can benefit health and wellbeing interventions, and that behavioral outcomes, in particular physical activity, may be the most ideal targets for gamification. With continued advances in wearable or transportable technologies (e.g., smart phones, smart watches, wireless activity trackers and other wireless devices) and the high prevalence of mobile phone use among children (5- to 15-year-olds spend an average of 15 h per week on a mobile phone [25, 26]), a need exists to harness the potential of mHealth lifestyle behavior modification interventions in the pediatric context, especially interventions targeting children 10 to 17 years of age.

To meet this need, an mHealth lifestyle behavior intervention—Aim2Be—was developed to promote healthy behaviors related to nutrition, physical activity, screen time, and sleep among children with overweight or obesity and their families. This paper describes our plan to assess the efficacy of Aim2Be in the context of a randomized controlled trial (RCT).

### Study aims and hypotheses

The primary aim of this RCT is to test the efficacy of Aim2Be with health coaching at improving weight outcomes and lifestyle behaviors among 10- to 17-year-old children compared to those randomized into a waitlist control condition. Children whose families receive the Aim2Be with health coaching are hypothesized to significantly decrease their age adjusted zBMI scores as well as significantly increase their moderate-vigorous physical activity, improve dietary behaviors (i.e., increase fruit and vegetable intake, improve dietary quality, and reduce sugar-sweetened beverage intake), and reduce screen time.

The secondary aims of the RCT are to 1) test whether supplementing the Aim2Be program with health coaching increases adherence to the intervention and 2) examine the mediators and moderators of adherence to the Aim2Be intervention. Given the exploratory nature of these aims, no hypotheses are stated.

## Methods/Design

### Study design

Two hundred Canadian children who have overweight or obesity and one parent for each will participate in the trial, which is taking place in 2019–2020. Most participants will be recruited for a study funded in part by the Public Health Agency of Canada with matched funds from partners. A portion of the participants (*n* = 60) will be recruited as part of a study embedded within a Canadian Institutes of Health Research (CIHR) Team Grant in Bariatric Care (Team ABC 3) [27]. After consent and baseline measurements, families will be randomized into one of two conditions: 1) intervention or 2) waitlist control. Families randomized into the intervention condition will receive the Aim2Be app with health coaching (i.e., receive tailored messages from a health coach with the option of scheduled and unscheduled text support). All participants will receive a package containing a scale, measuring tape, activity tracker (Fitbit), and a brochure with current health recommendations. At 3 months, families randomized to the waitlist control conditions will move to the intervention for months 3 to 6, but they will not be supported by the health coach. Data collection will occur at baseline, 3 months, and 6 months, utilizing REDCap (Research Electronic Data Capture) [28, 29] hosted at BC Children’s Hospital Research Institute (BCCHRI). Staff involved in the data collection and analysis will not be involved in delivering the intervention. Ayogo Health Inc. and the Childhood Obesity Foundation (COF) will deliver the Aim2Be intervention. The BCCHRI/School of Population of Public Health (SPPH) at the University of British Columbia (UBC) will collect and analyze the data. The study flow chart is shown in Fig. 1.

**Fig. 1 Fig1:**
[figure not shown]
Study flow chart

A computer-generated (www.sealedenvelope.com) randomization schedule will be used to allocate participants in blocks of four, six, or eight participants with a randomization ratio of 1:1 [30]. The allocation schedule will be concealed in the randomization module of REDCap and only assigned after informed consent and baseline assessments have been obtained. Research team members will not enter or modify the allocation schedule, as it will be entirely computer generated. Participants will not be blinded to their allocation conditions because participants will know whether they receive the Aim2Be intervention immediately or in 3 months. Allocation assignment will be concealed to the researchers at the analysis stage.

### Study participants

#### Inclusion and exclusion criteria

Child participants must be 10- to 17-years old and literate in English, able to read at the grade 5 level or above, and have a mobile phone or a computer with Internet access at home. Child participants must have either overweight or obesity, based on the World Health Organization cut-offs for children and adolescents aged 5 to 19 (BMI > 85th percentile). Parent participants must be the caregiver with whom the child primarily lives and must be literate in English.

Children must not have a diagnosis of any musculoskeletal, cardiovascular, pulmonary, or orthopedic problems; disabilities precluding the participant from being physically active; any other physical condition that precludes the participant from being physically active; diagnosis of anorexia nervosa or bulimia nervosa; diagnosis of type 1 diabetes; dietary restrictions or special diets that limit a participant’s ability to eat a variety of foods; simultaneous participation in another physical activity, nutrition, or weight management study/program; use of medication, nutritional supplements, or herbal preparations to help lose weight; pregnancy; or a history of psychiatric problems or substance abuse that would interfere with adherence to the study protocol.

#### Recruitment

Participants will be recruited using two main methods: clinical site referral and social media (i.e., Facebook advertisements with a link to a study site). Seven clinical weight management programs across Canada are participating in this study and include BC Children’s Hospital (Vancouver, BC), Alberta Children’s Hospital (Calgary, AB), Stollery Children’s Hospital (Edmonton, AB), Misericordia Community Hospital (Edmonton, AB), McMaster Children’s Hospital (Hamilton, ON), The Hospital for Sick Children (Toronto, ON), and Children’s Hospital of Eastern Ontario (CHEO) (Ottawa, ON). Clinical sites will use a combination of mailing and emailing invitation and information packages as well as telephone contact. All potential participants will be provided an invitational package that describes the study and includes copies of the consent and assent forms, as well as a link to the study website.

For both groups of potential participants, interested individuals will be asked to complete a secure, online consent to contact form in REDCap and provide their contact information. Individuals who express interest in the study will be screened via telephone for eligibility.

#### Consent/assent process

All participants will provide informed consent or assent prior to taking part in this study. All parent participants, with the exception of parents of children 16 years of age or older recruited from CHEO, will be asked to sign a consent form consenting to their own and their child’s participation in the study. Parents of children 16 years of age or older recruited from CHEO will be asked to sign a consent form agreeing to their own participation in the study. All child participants, with the exception of those 16 years of age or older recruited from CHEO, will be asked to sign an assent form agreeing to their own participation in the study. Child participants 16 years of age or older recruited from CHEO will be asked to sign a consent form agreeing to their own participation in the study.

### Sample size calculation

Based on previously published data [31], the RCT will have 80% power at an alpha of .05 to detect a .5 decrease in BMI z-score when the sample size in each group is 60. The BMI z-score was used to calculate sample size because this is the most difficult variable to change and requires the largest sample size of all of the primary outcomes. Based on this and accounting for both missing data and attrition, we project needing at least 80 families in each condition. However, to be able to detect a 20% difference in adherence (e.g., secondary aims outcome) between the two intervention groups (odds ratio of 2.33) at an alpha of .05 with 80% power using a one-sided t-test, 77 families are needed in each group. As the waitlist control group will receive the intervention at 3 months, we require 100 participants enrolled in each group (this accounts for 15% attrition from baseline to 3-month and the approximately 8% of families who will not download the Aim2Be app). Power calculations were conducted in nQuery (Statsols, USA). Based on these computations, we aim to enroll 200 participants in the RCT.

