### Statistical analyses

To address the primary aims, multilevel mixed-effect linear and logistic models, which account for the repeated nature of the data, will be used to test whether zBMI, dietary quality, fruit and vegetable intake, sugar-sweetened beverage intake, physical activity, and screen time at 3 months differ between Aim2Be and control condition participants. To address the secondary aim that examines whether health coaching influences adherence to the Aim2Be intervention, linear regressions will be used to compare the time spent using Aim2Be, number of days using Aim2Be, and number of tasks completed. Three analyses will be run, one for each adherence variables (i.e., time spent in app, numbers of days in app, and tasks completed). As the data are expected to be skewed, the dependent variables will be log-transformed or optimal transformation will be used to deal with the skewness of the data. Finally, examination of the mediators and moderators of adherence will use path analyses and relevant socio-demographic covariates and explore whether recruitment routes influenced adherence (e.g., self-referral or healthcare facility referral). Multiple imputation techniques will be used to deal with the missing data. Analyses will be conducted in Stata (StataCorp LLC, College Station, TX, USA) and MPlus (Muthen & Muthen, Los Angeles, CA, USA).

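### The 80% power behind the enrolled size of 200 belongs to a one-sided test of a binary adherence outcome that the plan never defines, and it does not carry over to the planned regressions

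*Protocol article*

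**What the plan says.** Four places in the protocol article bear on this.

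- **Sample size calculation, effect and test.** The zBMI calculation gives 60 per group, raised to at least 80 per condition for missing data and attrition. The article then sizes the coaching comparison on a 20% difference in adherence: "odds ratio of 2.33) at an alpha of .05 with 80% power using a one-sided t-test, 77 families are needed in each group".
- **Sample size calculation, inflation.** From there, "we require 100 participants enrolled in each group", and "this accounts for 15% attrition from baseline to 3-month and the approximately 8% of families who will not download the Aim2Be app". The adherence calculation, not zBMI, therefore sets the total of 200.
- **Study aims and hypotheses.** The first secondary aim asks whether adding coaching raises adherence. The section closes: "Given the exploratory nature of these aims, no hypotheses are stated".
- **Secondary outcomes and Statistical analyses.** Adherence is first measured as time in the app, days in the app and tasks completed. User profiles may become outcomes if the data vary enough. For the coaching question, "linear regressions will be used to compare the time spent using Aim2Be, number of days using Aim2Be, and number of tasks completed". There are three separate analyses, with a log or other transformation for skewness. The sidedness of these regressions is not stated.

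**The concern.** The sample size sentence and the analysis section describe different comparisons. A 20-point difference with an odds ratio needs each family classed as adherent or not, and the article gives no threshold or definition for that. The sentence is also mixed on its own terms, because it pairs an odds ratio with a t-test. The calculation is one-sided, while the aims section declines to state any hypothesis.

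This sentence is the stated reason for enrolling 200 families when 160 (2 × 80) would serve zBMI. It is also the only power statement for the coaching question. A reader could take a null coaching result as an answer with 80% power about a 20-point difference, in an outcome that was never defined. The effect that the trial can detect on the three measures it will analyse is not given.

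**Working it through.** **Inputs.** From the sample size section: difference 0.20, odds ratio 2.33, alpha 0.05 one-sided, power 80%, losses of 15% and about 8%. Allocation is "with a randomization ratio of 1:1" (Study design). The two adherence rates are not stated and have to be inferred.

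**1. Implied rates.** A 20-point gap with an odds ratio of 2.33 fits 50% vs 70%: (0.70/0.30)/(0.50/0.50) = 2.333. It fits 30% vs 50% equally well, with the same sample sizes by symmetry.

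**2. Reproducing 77 (one-sided).** z = 1.645 + 0.842 = 2.487, and its square is 6.183.

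- Means formula, SD 0.5: n = 2 × 0.25 × 6.183 / 0.04 = 77.3 per group. The exact t-test gives 77.97, so 78.
- Log odds ratio: n = 6.183 × (1/0.25 + 1/0.21) / (ln 2.33)² = 75.7, so 76.
- Pooled proportions: n = (1.645 × √0.48 + 0.842 × √0.46)² / 0.04 = 73.1, so 74.

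The stated 77 is therefore a one-sided figure, closest to the t-test form with SD 0.5.

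**3. Reproducing 100.** 77 / (0.85 × 0.92) = 98.5, and 77 / (1 − 0.23) = 100.0. In reverse, 100 × 0.85 × 0.92 = 78.2 analysable per arm. The inflation is sound.

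**4. The same binary contrast, two-sided 5%.** z = 1.960 + 0.842, squared 7.849.

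| Method | n per group for 80% | Power at 77 | Power at 78 |
|---|---|---|---|
| Pooled proportions | 93 | 72.1% | 72.6% |
| Log odds ratio | 97 | 70.8% | 71.4% |
| t-test, SD 0.5 | 100 (99.1) | 69.4% | 69.9% |

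**5. The planned regressions.** No SD or mean difference is given for any measure, so no single power figure exists. What can be stated is the detectable standardised difference d, treating each regression as a two-group comparison. At 77 per arm, two-sided 5% and 80% power, d ≈ 2.80 × √(2/77) = 0.45 (0.454 by the t distribution).

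Power at 77 per arm, two-sided 5%, for assumed values of d:

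| Assumed d | Power |
|---|---|
| 0.30 | 46% |
| 0.40 | 69% |
| 0.47 (50% vs 70% from cutting a logistic measure) | 82% |
| 0.50 | 87% |
| 0.52 (50% vs 70% from cutting a normal measure) | 90% |

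The normal case is d = z(0.70) − z(0.50) = 0.524. The logistic case is d = ln(2.33) × √3/π = 0.466. Power for the planned analyses therefore falls on either side of 80%, depending on an assumption that the document does not make.

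**The case against.** The strongest defence is that the arithmetic is correct for the test it names, and that the aim itself is worded in one direction, so a one-sided planning calculation fits it. An analysis plan that is not shown may settle the sidedness of the regressions. Adherence is only first defined as the three measures, and the possible user profiles mean that a categorical outcome is contemplated. The aim is openly exploratory, and the calculation only adds families, which helps the zBMI comparison.

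Most of this stands, and it limits the point. The directional wording softens the one-sided issue, although it sits uneasily with the absence of any hypothesis. The profiles do not rescue the odds ratio: they depend on the data and are not tied to the 20-point figure. An analysis plan could add detail, but the sample size sentence would still not describe the regressions that the article itself specifies.

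Two stronger readings are tempting, and the document supports neither.

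- A reader might infer that the 80% is false, or that the coaching comparison is underpowered. It is right for the one-sided binary test and merely unsupported for the regressions. Analysing a continuous measure can give more power than its dichotomised form, about 90% in the normal case above.
- A reader might infer that the trial's power is about 70%. That figure applies only if the undefined binary contrast is tested two-sided, which the article does not plan either.

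**Conclusion.** The point holds as an internal inconsistency of moderate severity. The calculation that moves enrolment from 80 to 100 per arm gives 80% power for a one-sided comparison of a binary adherence outcome, and the article neither defines nor analyses such an outcome. The 80% cannot be carried over to the three planned regressions. Their power is undetermined: 80% at a standardised difference of about 0.45, and less or more on either side of it.

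The 69–73% range for a two-sided binary test at 77–78 per arm rests on the inferred rates (50% vs 70%, or 30% vs 50%) and varies with the method. The 0.45 assumes a two-group comparison on a transformed scale, with alpha .05 for each measure separately. The zBMI calculation is untouched, and the aim is secondary and exploratory.

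**What to change.** Replace the adherence power sentence with one that matches the planned analysis. For example: about 77–78 analysable families per arm give 80% power, at two-sided alpha .05, to detect a standardised difference of about 0.45 on the transformed scale for each adherence measure.

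If the 20-point claim is kept, define the binary adherence outcome and its analysis before data are seen, give the two assumed rates and state the sidedness. If the test is two-sided, restate the power as about 70% (69–73% by method). The 30-minute split reported from the field test of the earlier app version should not be borrowed as that definition without justification: it graded engagement over 4.5 months in 14- to 17-year-olds.

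The cost is wording only. Enrolment stays at 200, and the zBMI calculation and the conduct of the trial do not change.

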### Development and description of Aim2Be

#### Aim2Be development

Aim2Be, which will be evaluated in this RCT, was built on the foundational knowledge learned in the first generation of the program called LiGHT (Living Green Healthy and Thrifty) and the second generation of the program, called Aim2Be version 1 (v1). LiGHT was an 11-module online program that integrated lifestyle behavior modification principles with environmental and financial concerns to address childhood obesity among 10- to 17-year-old children and their families [32]. Modest and nonsignificant improvements in readiness to change were initially observed for both the child and parents, likely due to ceiling effects on the measure and small sample size (*N* = 17 child-parent dyads). However, the qualitative feedback (*N* = 10 child-parent dyads) suggested that the LiGHT approach held promise. Specifically, both children and parents indicated that they related strongly to the foundational approach of the LiGHT intervention, meaning they liked having behaviors linked with health, environmental, and financial concerns. The evaluation also uncovered key areas that needed further improvement, including making the program more visually appealing, adding more interactivity, and creating a sense of community for the users.

The second generation of the intervention transitioned from a web-based intervention to a mobile app (iOs and Android) and was renamed Aim2Be. For those who do not have a smartphone, Aim2Be has remained accessible as a web-based platform via the internet. Aim2Be became a gamified app that supports children and their families to initiate sustainable behaviors in four primary areas: healthy eating, active living, reducing screen time, and healthy sleeping habits. It retained its focus on linking behaviors with health and living green, as well as adding emphasis on healthy body image and strong self-esteem. While Aim2Be retained some core elements from the LiGHT program, it 1) became strongly grounded in theories of behavior change (i.e., being family-based, supporting the development of self-regulatory skills at both the individual and familial levels, and enhancing self-efficacy through graded tasks) [10, 11, 19, 33]; 2) integrated principles of maintenance of health behaviors and as such it included self-regulatory processes that support intrinsic motivation [34–38]; 3) integrated gamification practices, which are designed to maximize both enjoyment and motivation [39]; 4) recognized the importance of body image and self-confidence in lifestyle management; 5) used the mHealth context to support self-regulatory processes [40]; 6) aligned with best clinical practices and guidelines in three areas (including a) the treatment of childhood obesity in Canada as it aligns with the curriculum of Canadian Weight Management programs (e.g., being family based, multi-behavioral, and focused on supporting skill development at the individual and familial levels); b) clinical guidelines for the management of childhood obesity as it integrates the central elements that need to be incorporated in these interventions (e.g., family focused, focused on improving lifestyle behaviors, skill based support) [41]; and c) Canadian health recommendations including the Canadian 24 Hour Movement Guidelines [42] and Canada’s Food Guide [43]); and 7) was designed specifically with and for children and their families (see details below).

Aim2Be was iteratively and incrementally developed. The first version of Aim2Be (v1) was field tested for 4.5 months among 301 teens between 14- and 17-years old and 315 parents. The quantitative evaluation revealed that teens who were moderately and/or highly engaged in the app (> 30 min of app usage) as compared to those with low engagement (≤ 30 min of app usage) significantly increased their motivation and self-efficacy to improve their dietary habits (i.e., limit sugar-sweetened beverages and increase intake of fruits and vegetables) and sedentary behaviors (i.e., limit screen time). At 4.5 months, children significantly increased their previous day’s intake of fruits and vegetables, decreased their consumption of 100% fruit juice, and reduced their screen time. In addition, parents who were more engaged with Aim2Be v1 reported significant improvements in the children’s dietary behaviors (i.e., increased intake of fruits and vegetables and decreased intake of sugar-sweetened beverages). Additionally, multiple rounds of qualitative evaluations were conducted among 36 teens/preteens and 24 parents. The qualitative evaluations included both focus groups and 2-week prototype testing, followed by semi-structured interviews. The results of these evaluations led to numerous improvements in Aim2Be including clarifying the overall purpose of Aim2Be, supplementing the tracking and check-in sections, adding more engaging features, and syncing the app with physical activity monitoring (i.e., Fitbit).

The conceptual framework of Aim2Be is shown in Fig. 2. At its core, the behavior change techniques (BCT) incorporated in Aim2Be are rooted in 1) Social Cognitive Theory (SCT) [44]; 2) the Player Experience and Need Satisfaction (PENS) model, which is an extension of the Self Determination Theory model for the gamified context and incorporates enjoyment to support intrinsic motivation and the basic psychological needs that promote intrinsic motivation (autonomy, relatedness, and competence/self-efficacy) [39, 45]; and 3) the ACUDO framework [46]. The ACUDO framework, is a best practice framework developed by Ayogo Health Inc. [46] to promote engagement and enjoyment by: a) supporting Agency, b) incorporating Challenges, c) infusing Uncertainty, d) supporting self-Discovery and exploration, and e) adding fun Outcomes such as rewards. Specifically, Aim2Be includes strategies that target 1) gamified mediators of behavior change to ensure the experience is both enjoyable and engaging; 2) behavioral mediators that aim to activate self-regulatory skills and support the development of intrinsic motivation and increase self-efficacy as a way to support behavior change and ultimately support healthy body weights; and 3) environmental mediators because it is recognized that behavior change needs to be physically and emotionally supported in the familial environment and that social support from both peers and/or coach is also important to changing health behaviors (see Fig. 2).

